### Scheme for trial analysis (Figure 2)

#### Ancillary study

An ancillary study of Human and Social Sciences will be performed entitled “Emotional and Cognitive Impact of Surgery and Peri-Operative Chemotherapy on Patients and Partners Diagnosed With a Gastric Adenocarcinoma”. The principal aim of this novel exploratory study is the longitudinal assessment of the emotional and cognitive state of the patient and partner according to allocated treatment arm. Evaluation will be by the following list of questionnaires (Quality of Life - QLQ-C30 and QLQ-STO-22 for the patient and SF-36 for partner, Emotional State – depression - CES-D and anxiety – STAI-Y-A for patient and partner, Emotional Adjustment – WCC for patient and partner, Perception of Disease – Brief-IPQ for patient and partner, Comprehension of Trial – ICEC-R for patient and partner, and Burden Assessment – CRA for patient and partner). Assessment will take place at 4 measured time-points – randomisation, day prior to surgery, prior to adjuvant treatment and on stopping adjuvant treatment. This study will allow to know better which therapeutic strategy, among the 3 compared, is the best for the patient’s and their partner’s quality of life and emotional state, which is determining in therapeutic decisions and compliance to treatments, what coping strategies promote the patient’s and their partner’s quality of life and emotional state the best. This result will be particularly interesting to improve the psycho-oncological care of the patient-partner couple: what perceptions the patient and their partner have about the disease and clinical trials, which are determining factors in therapeutic compliance, and that need to be known to improve psycho-oncological support in particular.

**Figure 2 F2:**
[figure not shown]
Scheme for trial analysis.

#### Ethical considerations

The study protocol was approved by the Institutional Review Board, the Nord Ouest IV ethics committee on the 15 of May 2012 and the Agence Nationale de sécurité des médicaments et des produits de santé (ANSM) on the 26 of June 2012 under the number 2012-000998-24. The institutional promoter is the University Hospital of Lille, France. The trial has been registered on the ClinicalTrial.gov website under the identification number NCT01717924. This study has received grant funding from the French National Cancer Institute (INCA) in 2011. The study complies with the Declaration of Helsinki rules and the principles of Good Clinical Practice guidelines. Informed consent will be obtained from each patient in written form prior to randomisation and an information leaflet will be given to each patient prior to inclusion in the study. Patient safety and all potential threats to patient safety will be monitored by an independent monitoring board which will be able, taking into account undesirable events and the level of post-operative mortality, recommend the discontinuation of one of the treatments evaluated.

## Discussion

Despite considerable advances in treatment, gastric cancer remains a disease with a poor prognosis. The heterogeneity of this disease, the distinct histological subtypes and the intrinsic molecular diversity represent a challenge and an opportunity in developing individually tailored therapy. The incidence of diffuse type GA, particularly SRC type has been increasing and SRCs represents 16% to 45.4% of GA in recent Western studies [5,7,8]. Tumours of SRC histology have several characteristics which differentiate them from other tumour types. They appear to affect patients at an earlier age [12,20], typically present with a more advanced tumour stage at diagnosis and carry a worse prognosis [12].

The advantage of perioperative treatment strategies for gastric cancer has been demonstrated in several phase III randomised controlled trials. The MAGIC study [9] conducted in the United Kingdom tested the potential efficacy, in 503 patients (stage ≥ II), of 3 cycles of neoadjuvant triplet chemotherapy using cisplatin, 5-fluorouracil and Epirubicin followed by surgery and three cycles of adjuvant chemotherapy compared with surgery alone for adenocarcinomas of the lower œsophagus and stomach. The results are well known, with a significant down staging in the chemotherapy arm in terms of size of tumour (p < 0.001) and a significant improvement in overall survival after 5 years (36% perioperative chemotherapy vs. 23% surgery alone, p = 0.009). This perioperative treatment regimen remains the standard of treatment in Europe. The FNCLCC ACCORD 07-FFCD 9703 trial [10] included 224 patients with an adenocarcinoma of the lower œsophagus and oesophago-gastric junction. Surgery alone was compared to perioperative chemotherapy with cisplatin and 5-fluorouracil, with results essentially confirming the findings of the MAGIC trial. The R0 resection rates were 87% and 74% respectively (p = 0.04) and the overall survival rate at 5 years was 38% vs. 24%, respectively, (p = 0.021). Neither of these trials performed a sub-group analysis for patients with a SRC. Further, preliminary data has suggested the need for a specific treatment strategy for SRCs because of a more advanced stage at diagnosis, with a greater prevalence of lymph node invasion and peritoneal carcinomatosis, a lower rate of R0 resection, earlier and more frequent disease recurrence and finally a worse overall prognosis [12].

Recently Messager et al [8] have published the results of a large multicentre comparative cohort study investigating the impact of peri-operative chemotherapy on survival in patients with SRC gastric tumours. It represents the largest study conducted on this histological subtype and involved analysis of 1050 patients diagnosed with SRC gastric tumours. No survival benefit was demonstrated for patients with SRC histology receiving peri-operative chemotherapy. Nor did neoadjuvant therapy result in tumour down-staging, down-staging of nodal disease, or decrease the disease recurrence. Indeed the authors found some evidence that disease progression during neoadjuvant treatment may have occurred in this subgroup of patients - extended resections were more commonly required and a longer median survival for patients treated with surgery alone prior to the incorporation of peri-oerative chemotherapy into the French guidelines for GA in 2006. This provides a clear imperative of the assessment of an alternative treatment strategy.

As several studies [11-14] have suggested a relative chemo resistance for SRC tumours and delay in definitive surgery may favour tumour progression [8] we hypothesise that a policy of primary surgery for SRC tumours, followed by adjuvant chemotherapy, will improve overall survival at 2 years when compared to a standard peri-operative chemotherapeutic strategy. This primary outcome criteria is justified as it provides a short term evaluation criteria (important in view of the very poor prognosis associated with this disease) and survival at 24 months has been found in a multicentre retrospective series of over 1000 patients to be significantly different (27% vs. 10%) [8].

This randomised trial will provide high level evidence regarding the value of a strategy of primary surgery for SRC gastric tumours. Whilst the development of new biomarkers and associated targeted therapies are awaited to individualise gastric cancer therapy, the results of this trial should will help further in devising individualised protocols of patient care in a tumour group whose diversity increasingly demands assessment of alternative strategies.

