To support these observations and establish more reliable data regarding the behaviour of SRC tumours, at the start of 2010 our team launched a French retrospective multicenter study of all consecutive oesophagogastric adenocarcinomas in 19 centres in France treated between January 1997 and January 2010 (ADCI001) [8]. Amongst 3010 patients registered 1050 (34.9%) had a SRC tumour, with 126 being metastatic at diagnosis and excluded from the study. The remaining 924 patients underwent an intention to treat analysis according to whether they underwent primary surgery (n = 753, 81.5%) or neoadjuvant chemotherapy (n = 171, 18.5%). Multivariate analysis showed pre-operative chemotherapy to be an independent predictor of poor survival (HR = 1.4, 95% CI 1.1-1.9, p = 0.042), with overall survival at 2 years of 27.1% in the primary surgery group versus 12.3% in patients treated with neoadjuvant chemotherapy. Hence, increasingly data is suggestive of SRC chemo resistance, and a deleterious effect of delaying definitive surgery for an ineffective treatment whose toxicity may cause host immunosuppression facilitating disease progression.

There is therefore clear impetus for a prospective randomised study to evaluate the appropriate perioperative therapeutic strategy for SRCs.

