## Methods/design

### Protocol overview

PRODIGE-19-FFCD1103-ADCI002 is a prospective multicentre controlled randomised phase II/III trial comparing current standard of care (2x3 cycles of perioperative Epirubicin, cisplatin, 5-fluorouracil (ECF) chemotherapy) with a strategy of primary surgery followed by adjuvant ECF chemotherapy (6 cycles) in patients with a SRC tumour and eligible for curative surgery. In phase II patients will be randomised using minimisation with stratification criteria – centre, tumour stage, performance status and tumour localisation. The principal objective will be to determine if the experimental arm (primary surgery followed by adjuvant chemotherapy) has a sufficient interest in terms of percentage of living patients at 24 months to be evaluated in a phase III trial. If ≤10% of patients in the experimental arm is alive at 24 months, phase III will not be initiated. Recruitment will be postponed for a 6 month period after the completion of phase II of the study to allow for the interim analysis of data. The primary objective of phase III will be to demonstrate the superiority of the experimental arm in terms of overall survival. The study is planned for a total duration of 10 years and is registered on clinicaltrial.gov website (NCT01717924).

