### Statistical evaluation and sample size calculation

Phase II– The phase II part of this trial will determine the percentage of patients in the experimental limb of the study (group B) who are alive at 24 months and thus validate the interest pursuing the evaluation of a strategy of primary surgery in a subsequent phase III trial. To demonstrate the interest of the experimental arm of this study, it will be necessary to include 40 in each treatment arm, with a unilateral alpha error of 5% and a power of 85%. Taking into account a 5% level of loss to follow-up, 84 patients will be included in total (42 in each treatment arm). If 7 or less patients are alive after 24 months, then the treatment B will be considered not interesting. Survival data for patients from phase II of this trial will allow for the readjustment of the number of patients required to be enrolled in the phase III trial according to the adaptive trial design.

Phase III – The objective of the phase III trial will be to demonstrate the superiority of group B and the principal outcome criteria will be overall survival. To demonstrate a desired 10% difference in overall survival in favour of group B at 24 months, with a bilateral alpha error of 5% and a power of 85%, it will be necessary to observe 291 deaths. With an estimated rate of inclusion of 6 patients per month, with a 5% rate of loss to follow-up and surveillance of the last included patient of 24 months, a total of 314 patients will have to be recruited. On this basis 230 additional patients will need to be recruited after the completion of phase II.

Two intermediate analyses are planned, one for Phase III sample size read justement and the second one to allow for the early identification of the superiority of group B. The first intermediate analysis of survival data will take place at the end of phase II. The second intermediate analysis will be performed after either 175 deaths or 60% of events have occurred.

Statistical analysis for phase II will be performed on a modified intention to treat population meaning all patients who can be evaluated and who are not lost to follow up at 24 months. For phase III, analysis of the main criteria will be performed on an intention to treat (ITT) principle. The per-protocol population will be defined as the ITT population having no major deviation or major of the protocol.

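### The same cohort's 24-month survival with preoperative chemotherapy is given as 12.3% and as 10%; the 291 deaths fit only about 10%, and at 12.3% they give about 81% power, not 85%

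*Protocol article*

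**What the plan says.** Two sections of the protocol article report 24-month survival from one multicentre retrospective cohort (reference 8).

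- Background: "overall survival at 2 years of 27.1% in the primary surgery group versus 12.3% in patients treated with neoadjuvant chemotherapy".
- Discussion, in support of the primary criterion: "survival at 24 months has been found in a multicentre retrospective series of over 1000 patients to be significantly different (27% vs. 10" per cent.

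In the section Statistical evaluation and sample size calculation, phase III aims at a 10-point difference in survival at 24 months in favour of group B, with two-sided 5% error and 85% power, for which "it will be necessary to observe 291 deaths". Total recruitment is 314 patients. Neither the control rate nor the hazard ratio behind the 291 is given.

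For phase II, the Protocol overview says: "If ≤10% of patients in the experimental arm is alive at 24 months, phase III will not be initiated". The sample size section adds that "it will be necessary to include 40 in each treatment arm, with a unilateral alpha error of 5% and a power of 85" per cent, and that "If 7 or less patients are alive after 24 months, then the treatment B will be considered not interesting".

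**The concern.** Rounding explains 27.1% becoming 27%. It does not explain 12.3% becoming 10%, and the article mentions no other subset, time point or analysis that would. This matters beyond the literature review because an absolute gain of 10 points is not a fixed treatment effect. The higher the control survival, the closer to 1 the hazard ratio that 10 points represents, and the more deaths are needed to detect it. If the 291 deaths were derived from one of the two figures and the other is correct, the stated 85% power does not apply to the stated target.

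**Working it through.** **Inputs.** From the sample size section: 10-point difference at 24 months, two-sided 5%, power 85%, 291 deaths, 314 patients; for phase II, 40 per arm, one-sided 5%, stop at 7 or fewer alive. Control rates: 12.3% (Background) and 10% (Discussion; also the no-go level in the Protocol overview). Exponential survival or proportional hazards and 1:1 allocation are assumed.

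**Formulas.** For control survival p and group B survival p + 0.10 at 24 months:

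- HR = ln(p + 0.10) / ln(p)
- Schoenfeld: deaths = 4(z₀.₉₇₅ + z₀.₈₅)² / ln(HR)²
- Freedman: deaths = (z₀.₉₇₅ + z₀.₈₅)² × [(1 + HR)/(1 − HR)]²
- (z₀.₉₇₅ + z₀.₈₅)² = (1.960 + 1.036)² = 8.978

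**Step 1: reproduce the 291.** At 10% to 20%, HR = ln 0.20 / ln 0.10 = 0.699.

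- Schoenfeld: 4 × 8.978 / 0.358² = 280
- Freedman: 8.978 × (1.699/0.301)² = 286

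The Freedman figure is within 2% of 291. Inflating it by 1.0156 for one O'Brien-Fleming-type look at 60% of events gives 290.5, that is 291. That boundary is an assumption, since the article names none.

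Solving backwards, 291 deaths at 85% power correspond to HR 0.701 (Freedman) or 0.704 (Schoenfeld). With a 10-point gain these imply control rates of 10.3% and 10.6%. A control rate near 60% would give a similar HR (ln 0.70 / ln 0.60 = 0.698), but 291 deaths among 314 patients (93%) rules it out.

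**Step 2: repeat at 12.3%.** At 12.3% to 22.3%, HR = ln 0.223 / ln 0.123 = 0.716.

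| Control → group B | HR | Deaths, Schoenfeld | Deaths, Freedman | Power with 291 deaths |
|---|---|---|---|---|
| 10% → 20% | 0.699 | 280 | 286 | 86.3% / 85.6% |
| 12.3% → 22.3% | 0.716 | 322 | 328 | 81.3% / 80.6% |

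The power by Schoenfeld in the second row is Φ(√291 × 0.334/2 − 1.960) = Φ(0.889) = 0.813. With the assumed interim look the requirement becomes 327 to 333 deaths and the power about 80% to 81%. Even 322 deaths exceeds the 314 patients planned, so longer follow-up alone could not supply them.

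**Step 3: a target stated as HR 0.70.** With 291 deaths, power is Φ(17.06 × 0.357/2 − 1.960) = 86.0% (Schoenfeld) or Φ(17.06 × 0.30/1.70 − 1.960) = 85.3% (Freedman).

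**Step 4: phase II, exact binomial, go if 8 or more of 40 are alive.**

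| True 24-month survival in group B | Probability of proceeding |
|---|---|
| 10% | 4.2% |
| 12.3% | 11.1% |
| 26% | 85.3% |
| 27.1% | 88.5% |

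At 10% the rule meets the stated 5%. Power is at least 85% from 26% upwards.

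**The case against.** **Neither figure is labelled a planning value.** This is true. The Background is context, and the Discussion uses its figure to justify the endpoint. A journal article may leave the planning baseline to the full protocol, so its absence is not itself a fault. What stands is that one quantity from one source has two values, and that the stated 291 deaths agree with only one of them. The Discussion speaks of more than 1000 patients while the Background's 12.3% comes from an analysis of 924, so a different subset is conceivable, but the article does not say so.

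**The shortfall is modest and conditional.** It exists only if the target remains 10 points above a 12.3% control rate. The cohort's own contrast, 12.3% to 27.1%, is HR 0.623, for which 291 deaths give about 98% power. The 12.3% is also imprecise: read as 21 of 171 patients, ignoring censoring, its 95% interval runs from about 8% to 18% and includes 10%. Both points limit the size of the problem. Neither makes 85% the right power for a 10-point gain from 12.3%.

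**Phase III will be resized after phase II.** The plan provides for this, and it may remove the shortfall. The readjustment still needs a stated starting rate and hazard ratio.

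**A stronger reading of phase II.** A reader might infer that the phase II error is 11% rather than 5%. The documents do not support that. The error rate is defined at the chosen null. The Protocol overview names 10%, the rule concerns group B alone, and nothing claims 5% error against the control strategy's historical survival. The 11.1% is the chance of proceeding at a different true rate. Phase II power is also intact, and the phase III type I error does not depend on the control rate.

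**Conclusion.** The inconsistency is real and bears on a number the trial relies on. The 291 deaths correspond to a control rate of about 10%. If 12.3% is correct and the 10-point target is kept, phase III power is about 81% instead of 85%, and 322 to 328 deaths would be needed. This rests on proportional hazards with roughly exponential survival, equal allocation, and standard event formulas. Which of the two figures is correct cannot be settled from the article. The effect is confined to phase III power and may be eased by the planned readjustment, so this is an inexpensive correction of a figure and not a failure of the design in both phases.

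**What to change.** 1. Check the cohort's report and give one figure in both the Background and the Discussion. If the two describe different subsets or analyses, say so.
2. Beside the 291 deaths, state the control rate at 24 months and the implied hazard ratio.
3. If the figure is 12.3%, choose one of two statements: power of about 81% for 12.3% to 22.3%, or a target of HR 0.70, for which 291 deaths give about 85% to 86%. A target stated as a hazard ratio also keeps the event number valid if control survival differs from plan.
4. Carry the reconciled rate into the sample size readjustment after phase II. If 85% power for 10 points above 12.3% is wanted, this is the place to plan for it, because it cannot be reached with 314 patients.
5. Leave the phase II error as stated. At most, add for information that the chance of proceeding would be about 11% if group B's true survival were 12.3%.

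The cost is wording and, under the first option in item 3, a less favourable stated power. Items 1 to 3 and 5 need no extra patients.

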## Abbreviations

GA: Gastric adenocarcinoma; SRC: Signet ring cell; ECF: Epirubicin, cisplatin, 5-fluorouracil; EUS: Endoscopic ultrasound; OS: Overall survival; DFS: Disease free survival; FFCD: Fédération Francophone de Chirurgie Digestive; CEA: Carcinoembryonic antigen; CA: Carbohydrate antigen; PCEA: Patient controlled epidural analgesia; PCA: Patient controlled analgesia; CT: Computerised tomography; QoL: Quality of life; EORTC: European organisation for research and treatment of cancer; 95% CI: 95% confidence interval; WHO: World Health Organisation; cTNM: Clinical tumoural staging; NCI CTC: National Cancer Institute Clinical Toxicity Criteria; ANSM: Agence Nationale de sécurité des médicaments et des produits de santé; SFCD-ACHBT-HAS-INCA: Société Française de Chirurgie Digestive – Association Française de Chirurgie Hépato-Biliaire et de Transplantation Hépatique - Haute Autorité de Santé – Institut National de Cancer.
